## Abstract

**Background:**

The benefits of e-health support for dementia caregivers are becoming increasingly recognized. Reaching early-stage dementia caregivers could prevent high levels of burden and psychological problems in them in the later stages of dementia. An iterative step-wise approach was employed to develop the blended care self-management program “Partner in Balance” for early-stage dementia caregivers. The design of a study evaluating the process characteristics and effects is presented.

**Methods/design:**

A mixed-method, single-blind, randomized controlled trial with 80 family caregivers of community-dwelling people with (very) mild dementia will be conducted. Participants will be randomly assigned to either the 8-week blended care self-management program “Partner in Balance” or a waiting-list control group. Data will be collected pre intervention and post intervention and at 3-, 6- and 12-month follow-ups. Semi-structured interviews will be conducted post intervention. A process evaluation will investigate the internal and external validity of the intervention. Primary outcomes will include self-efficacy and symptoms of depression. Secondary outcomes will include goal attainment, mastery, psychological complaints (feelings of anxiety and perceived stress), and quality of life. Possible modifying variables such as caregiver characteristics (quality of the relationship, neurotic personality) and interventional aspects (coach) on the intervention effect will also be evaluated. A cost-consequence analysis will describe the costs and health outcomes.

**Discussion:**

We expect to find a significant increase in self-efficacy, goal attainment and quality of life and lower levels of psychological complaints (depression, anxiety and stress) in the intervention group, compared with the control group. If such effects are found, the program could provide accessible care to future generations of early-stage dementia caregivers and increase dementia care efficiency.

**Trial registration:**

Dutch trial register NTR4748.

**Electronic supplementary material:**

The online version of this article (doi:10.1186/s13063-016-1351-z) contains supplementary material, which is available to authorized users.

## Background

Family caregivers are currently becoming the main source of care for people with dementia [1]. However, dementia caregivers are at risk for depression, anxiety and other health problems [2]. Interventions aimed at reducing their burden of care might reduce dementia care costs in the long term if institutionalization can be postponed [3].

Many face-to-face caregiver support interventions have proven to be effective on caregiver distress (random effect size = 0.3), caregiver knowledge (random effect size = 0.5) [4], and self-efficacy (effect sizes ranging from 0.3 to 0.9) [5], but the expected future increase in the number of people with dementia raises concerns about whether care professionals can cope with this demand [6]. E-health interventions could serve as cost-effective alternatives for dementia caregiver support [7–9], both increasing caregivers’ access to support and extending the reach of such support [10–13]. The benefits of e-health are becoming increasingly recognized, and remote support for dementia caregivers is growing [14–16].

Previous e-health studies on dementia caregivers show positive effects on caregiver confidence, stress, depression, and self-efficacy with effect sizes ranging from 0.2 to 0.3 [17]. Provision of tailored information, a coach, and the opportunity to interact with other caregivers shows the most promise [17]. Blending face-to-face guidance with online modules increases caregivers’ connection with the therapist and adherence [18, 19]. However, research on the effects of e-health on dementia caregivers lacks methodological rigor [17], and adverse effects of caregiving are often addressed in the later stages of dementia, when caregivers already feel overburdened [20]. Despite their low levels of life satisfaction and high levels of overload, caregivers do not use services in the early stages because they do not feel the need for such services or because they struggle with acceptance due their experience of stigma [20–22]. Supporting caregivers in the early stages of dementia could prevent high levels of burden and psychological problems in them in the later stages and delay institutionalization [23–26]. However, early-stage dementia caregiver support can be experienced adversely if the care does not suit the caregiver’s personal situation or the stage of the disease. Negative and stigmatizing information can make it difficult for caregivers to identify with and may hamper acceptance [20]. Learning to positively manage life with dementia, instead of managing the dementia itself in a self-management program, could facilitate caregivers’ adaptation to their new caregiving role. A focus on enhancing positive, intact experiences that are tailored to the individual caregiver’s situation may be more effective in increasing caregiver self-efficacy and reducing the negative consequences of caregiving at the later stages [20].

### Study aim and hypotheses

The current paper presents the design of a randomized waiting-list controlled trial investigating the effects of the blended care self-management program “Partner in Balance.” Alongside the effectiveness study, a process evaluation will be conducted to evaluate internal and external validity. As recommended by the Medical Research Council (MRC) Framework for the design and evaluation of complex intervention [27], the program was based on existing literature [17], theory, and user and professional input [28]. In a pilot evaluation, caregivers reported increased feelings of self-efficacy and goal attainment post intervention. Feedback from the feasibility study was used to adapt the intervention to increase user-friendliness [28]. The next objective is to evaluate the process characteristics, effectiveness and cost-consequence of “Partner in Balance.” Specifically, we aim to investigate (1) the internal and external validity of the intervention based on sampling quality (recruitment, randomization and reach) and intervention quality (relevance, feasibility, and performance according to protocol) prior to the effect analysis to evaluate credibility and generalizability [29], (2) whether “Partner in Balance” is superior to the waiting-list control condition in terms of participants’ subjective well-being, as evidenced by improved subjective self-confidence (increased self-efficacy) and goal attainment and lower levels of psychological complaints (depression, anxiety and stress) following the self-management intervention, and (3) whether these effects are maintained after 3, 6 and 12 months, and lastly (4) the cost-consequence of “Partner in Balance” is calculated to estimate the impact of the intervention on resource use, costs, and health outcomes.

## Methods

The Medical Ethics Committee of the Maastricht University Medical Center + (MUMC+) approved this study (#12-4-059). The study is a randomized waiting-list controlled trial that was designed to maximize acceptability and adherence to the research protocol in the control group and minimize attrition effects. Data will be collected pre intervention and post intervention and at 3-, 6- and 12-month follow-ups. See Fig. 1 for the flow diagram. A full copy of the Standard Protocol Items: Recommendations for Interventional Trials (SPIRIT) checklist for study protocols can be found in Additional file 1.

**Fig. 1 Fig1:**
[figure not shown]
Consolidated Standards of Reporting Trials (CONSORT) flow diagram

### Population

#### Recruitment

The study population will consist of family caregivers of community-dwelling people with (very) mild dementia of all subtypes (Clinical Dementia Rating (CDR) score 0.5–1) [30]. No age limit will be applied; however, only adult family caregivers will be solicited. Participants will be recruited from memory clinics (MUMC+, Elkerliek Hospital Helmond, Catharina Hospital Eindhoven) and ambulatory mental health clinics (Virenze-RIAGG Maastricht, MET GGz Roermond) in the south of The Netherlands. Caregivers will be approached by the clinician or therapist who is treating their family member. Prior to participating, caregivers will provide written informed consent.

#### Eligibility

Family caregivers of people with (very) mild dementia of all subtypes (CDR score 0.5–1) who are aged over 18 years, have access to the Internet at home, and have basic skills in the use of computers are eligible to participate in the study. Potential participants who have insufficient cognitive abilities to engage in the online self-management program; are overburdened or have severe health problems, as determined by study staff; or care for people with dementia caused by human immunodeficiency virus (HIV), acquired brain impairment, Down syndrome, chorea associated with Huntington’s disease, or alcohol abuse will be excluded from participation.

### Randomization

Following the baseline assessment, participants will be randomly assigned to either the self-management intervention or the waiting-list control group using a computer program operated by an independent statistician. Block randomization will be conducted to reduce the risk of unbalanced assignment to the experimental and control groups. We will use randomly permuted blocks and several block sizes (4, 6 and 8). The block size and order of allocation will be randomly chosen at the beginning of each block. This reduces the risk of predicting group assignment and keeps research staff blind to the randomization process. An independent research assistant who is unknown to the allocation of the treatment will conduct the post-intervention and follow-up assessments, and will be asked to evaluate the success of blinding, and reasons for possible unmasking, on the Case Record Form.

### Intervention

#### Experimental group

The “Partner in Balance” intervention consists of a face-to-face intake session with a personal coach, an online period, and a face-to-face evaluation session with the personal coach. The basis of the intervention is learning to identify areas of change and creating personal goals. The development and final intervention are described in detail elsewhere [26]. The goal of the intake session is to familiarize participants with the program and to set goals that they wish to accomplish through their participation using the motivational interviewing technique frequently used to identify change objectives and enhance intrinsic motivation to change [31]. Goals and strategies to achieve these goals are individually determined and depend on the participants’ personal problems, motivation, and capabilities. Given that it is not usual for the elderly to reflect on their problems or concerns thematically, a “toolbox” of themes should be developed to aid the discussion of these issues with the participants [32]. Based on their personal needs and areas of interest, participants will select four out of nine modules in the toolbox, and they will be briefed individually to ensure that they understand the online procedure. The module themes are provided in Table 1. The module contents are described elsewhere [28]. Following the intake, participants will complete their chosen modules online during an 8-week period. Two weeks are allocated for each module, but participants will be allowed to complete the modules at their own pace in accordance with the self-management approach [33]. After the online period, participants will meet with their coach face-to-face to discuss their ability to accomplish goals and cope with future difficulties. Participants will continue to have access to their personal page and modules after the intervention period.

**Table 1 Tab1:** Themes of the available 'Partner in Balance' modules

“Partner in Balance” modules 1. Acceptance 2. Balance in activities 3. Communication with family member and environment 4. Coping with stress 5. Focusing on the positive 6. Insecurities and rumination 7. Self-understanding 8. The changing family member 9. Social relations and support	

#### The personal coach

The personal coach is an experienced professional (psychologist or psychiatric nurse) from one of the participating sites. Coaches will receive a 1-day training on self-management techniques and online help before the start of the intervention. They will receive supervision from an experienced professional in the fields of psychology and self-management to ensure high-quality feedback.

Coaches support participants in choosing modules that fit their situation, help identify feasible goals, offer techniques to achieve goals and provide general constructive feedback on their assignments. Coaches will be matched with the participants assigned to them via a personal login code.

#### Control group

Participants in the control group will be placed on a waiting list for 8 weeks. After they complete the post-test assessment, they will receive the online self-management intervention. They will receive the same pre-test and post-test attention from the research team as the experimental group.

### Procedure

Participants will be assessed at five time points: (T_0_) baseline assessment, (T_1_) post-intervention or waiting-list assessment (8 weeks), (T_2_) post-intervention assessment for waiting-list (8 weeks after T_1_), (T_3_) 3-month follow-up, (T_4_) 6-month follow-up, and (T_5_) 12-month follow-up. Figure 2 shows the schedule of enrollment, procedures and mixed-method assessments per condition.

**Fig. 2 Fig2:**
[figure not shown]
Schedule of enrollment and assessments per condition

### Questionnaires

#### Primary outcomes

The *Caregiver Self-efficacy Scale (CSES)* [34] is based on a Dutch version of the self-efficacy instrument devised by Lorig et al. [35] and measures care management self-efficacy (four items) and service-use self-efficacy (five items). Item scores range from 1 (not at all certain) to 10 (very certain). Total care management self-efficacy scores range from 4 to 40 and service use self-efficacy from 5 to 50. Good reliability was demonstrated for the CSES in a previous study [28].

The Dutch version of the *Center for Epidemiological Studies Depression Scale (CES-D)* [36] consists of 20 items that rate the frequency of depressive symptoms during the past week, with higher total scores indicating greater depressive symptoms. Scores range from 0 (rarely or none of the time (less than 1 day)) to 3 (most or all of the time (5 to 7 days)). The total score ranges from 0 to 60. Items represent depressed mood, feelings of guilt and worthlessness, feelings of helplessness and hopelessness, psychomotor retardation, loss of appetite, and sleep disturbance. The CES-D is sensitive to changes in caregiver depressive symptoms after intervention [37].

#### Secondary outcomes

*Goal attainment scaling (GAS)* [38] is a measure of treatment-induced change. GAS enables comparisons of individuals’ relative success in achieving goals that are individually determined. Scores range from −2 (much less than expected) to +2 (much better than expected), with 0 indicating that the goal is attained. Raw scores are transformed into *T*-scores [39]. *T*-scores include attainment level and a potential weight assigned to the goal(s). *T*-scores of ≥50 indicate effective goal attainment. GAS has demonstrated reliable monitoring of progress over time [40].

The *Pearlin Mastery Scale (PMS)* [41] measures perceived control, otherwise known as mastery. The scale includes seven items, with scores ranging from 1 (completely agree) to 5 (completely disagree). The sum score (range 0–35) indicates the extent of perceived control or mastery, with higher scores indicating greater perceived control. The psychometric properties of the Dutch version of the PMS have found to be good in previous studies [42].

The *Perceived Stress Scale (PSS)* [43] measures overall appraisals of stress in the past month. Ten items on unpredictability, control and overload are rated on a 5-point scale from 0 (never) to 4 (very often), with higher total scores indicating higher levels of stress. The scale showed good reliability [44].

The *Hospital and Anxiety Depression Scale (HADS-A)* [45] is used to generate scores for generalized anxiety. The anxiety subscale consists of seven items rated from 0 (not at all) to 3 (a great deal of the time). Total scores range from 0 to 21, with higher scores indicating more anxiety. Good reliability was found [46].

The *Investigating Choice Experiments for the Preferences of Older People CAPability measure for Older people (ICECAP-O)* [47] measures five important attributes of quality of life. The value system for the 1024 states defined by the instrument was derived from a survey of older people in England, using a best–worst scaling valuation method. The value system provides a single summary score, anchored at 0 (“no capability”) and 1 (“full capability”), for each state described in terms of the five attributes. The ICECAP-O may have the potential to measure broader outcomes and be more sensitive to differences between intervention and comparators than the EuroQol five dimensions questionnaire (EQ-5D), which is often used in cost-effect evaluations [48].

#### Additional measures

Quality of the relationship is rated with four items of the *University of Southern California Longitudinal Study of Three-Generation Families measures of positive affect* [49]. The items indicate (1) general closeness, (2) communication, (3) similarity of views about life, and (4) degree of getting along. Scores range from 1 (not at all) to 4 (very). The value system for the 1024 states uses a best–worst scaling valuation method, providing a single summary score, anchored at 0 (“no capability”) and 1 (“full capability”). Good reliability was found in a previous study [50].

The *NEO Five-Factor Inventory (NEO-FFI)* [51] measures personality. The 12-item Neuroticism domain will be used to identify individuals who are prone to psychological distress. This domain assesses six traits: anxiety, angry hostility, depression, self-consciousness, impulsiveness and vulnerability [52]. The reliability of the Dutch version of the NEO-FFI is good [51].

#### Semi-structured interview

After the intervention has been completed, a semi-structured interview will be conducted to qualitatively evaluate the effect of the program on participants’ self-efficacy. The interview will take place face-to-face in the caregiver’s home or at the participating institution and will be audiotaped with the participants’ permission. Topics include the application of the intervention in daily life and the intervention’s impact on knowledge about the disease, caregiver functioning, and self-esteem.

#### Process outcomes

Prior to the analysis of effects, the internal and external validity of the intervention will be evaluated using data on sampling quality (recruitment, randomization, and reach) and intervention quality (relevance, feasibility, and performance according to protocol) to provide essential information on the program’s credibility and generalizability [29]. A description of the recruitment and randomization procedure, the informed consent and allocation procedure, and the barriers and facilitators to recruiting caregivers will be provided. Reach will be determined by the proportion of caregivers participating in the study and the number of institutions involved in the intervention. Intervention quality will be determined on two levels: (1) coach, and (2) participant. Data will be collected from the research database, and during focus group interviews with coaches and individual semi-structured interviews with participants post intervention. Coaches will be asked to complete a questionnaire about clearness, relevance, and usability of the intervention. Delivery of the intervention according to protocol will be evaluated with a structured registration form (Additional file 2). For an overview of the specific methods used for each aspect of validity, see Table 2.

**Table 2 Tab2:** Methods used to assess process of the intervention

Process aspects	Methods used
Sampling quality	Procedure of recruitment, informed consent, and allocation; recruitment barriers and facilitators; reach (proportion participants/institutions)
Intervention quality (rated by coach)	
Protocol deviations; amount and intensity of contact with participant	Registration form (Additional file 2)
Relevance for caregivers and professional coaches; usability in daily practice	5-point rating scale^a^
Advantages of the program; disadvantages/suggestions for improvement; recommendation to other professionals	Open-ended questions
Intervention quality (rated by participant)	
Number of online visits and time spent per module	Online system usage data^b^
Compliance to the program	Ratio number of modules chosen/completed
Clarity of the content; website ease of use; satisfaction with online aspect combined with face-to-face contact; satisfaction with personal coach and feedback; advantages of the program; disadvantages/suggestions for improvement; impact on understanding and knowledge; impact on caregiver self-esteem; recommendation to other caregivers	Semi-structured interview

^a^1 = totally disagree to 5 = totally agree

^b^Online system usage data include frequency of logging in to the system, length of visit (per module feature), and time and date of visit

#### Intervention costs

To provide a comprehensive presentation of the value of “Partner in Balance,” a cost-consequence analysis will be conducted. This is a listing of all the relevant costs and consequences (outcomes) of the intervention. Costs will be based on the Dutch guidelines for cost calculations in health care [53]. Formal and informal resources used by the caregiver and care recipient will be mapped by means of the Resource Utilization in Dementia – shortened version (RUD-lite) [54], which includes information on hospital costs, contacts with the GP or other health care professionals, home care, day care, admissions to a nursing home or home for the elderly, medication and acquisition of goods/aids. Costs are calculated by multiplying the volume of resource use by the cost price per resource unit and include the period from the baseline assessment up to the last follow-up measurement (12 months). Intervention costs include time spent on the intake and evaluation session, e-mail contact, the coach training sessions, materials, and coach supervision. The coaches will register the amount of time spent on the intake, evaluation session and e-mail contact on a structured registration form. All costs are expressed in Euros and are adopted from Hakkaart-van Roijen [53].

### Sample size

We determined our sample size based on previous online intervention studies on caregivers of people with dementia using the CSES as outcome measure, the use of repeated measures, within-between interaction with a mean effect size of 0.2 [55], the following assumptions: alpha 0.05, power 85 % and 25 % loss to follow-up. In accordance with these criteria, we aim to enroll 80 participants (40 participants per group).

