### Statistical analyses

#### Quantitative measures

Prior to the analysis, data will be checked for missing values, outliers, and normality. Possible differences between the study groups’ baseline characteristics will be tested with *t* tests for continuous variables and χ^2^ tests for categorical variables. In case of missing data, we intend to test if data is missing completely at random (MCAR) based on a comparison of the baseline characteristics of study completers and participants with missing values. If *p* <0.05 for (one of) the variables in the model, the missing values are non-random. In case of data MCAR, the specification of a missing value or dropout model is not necessary and list-wise deletion will be applied. In case of missing data not at random, we will apply a multiple imputation-based strategy [56].

To examine differences in the outcomes of the intervention and the waiting-list control groups during the intervention period, an analysis of covariance (ANCOVA) will be conducted with post-intervention outcome as the dependent variable, intervention (“Partner in Balance,” waiting-list control group) as the between-subjects variable and the pre-intervention outcome, emotional instability, quality of the relationship, educational level and relationship to the care recipient as covariates. Each outcome will be assessed as a dependent variable. Group differences in the post-intervention outcome adjusted for its baseline value will be examined to test the primary hypothesis. If differences are found, the inter-group effect size will be calculated according to Cohen’s *d*.

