To analyze changes in the primary and secondary outcomes during the total study period, the data from the intervention-only group and the waiting-list group receiving the intervention after 8 weeks will be combined using a linear mixed model (LMM). The LMM will estimate fixed effects (regression slopes) for the change during the waiting-list interval (T0–T1 as measured in the waiting-list group only) and fixed effects for change in the intervals during (T1–T2) and after (T2–T3, T3–T4, T4–T5) the intervention period (measured in the waiting-list group after the first 8 weeks and in the intervention group). This will allow us to compare the rate of change in those receiving no intervention (T0–T1) with those receiving the intervention (T1–T5) while accounting for the fact that data are nested in individuals and, therefore, correlated. Intervals will be entered as a categorical variable (five levels) using dummies. Model fit of models with random intercepts (at the participant level) and models with random intercepts and random slopes (at the interval level) will be compared using likelihood ratio tests.

Emotional instability and quality of the relationship will be included as covariates because they are expected to influence the difference between groups. Coach will be introduced into the analysis as a random factor to estimate the variability attributable to the coach. For goal attainment, descriptive statistics will be used to calculate the total number of goals set per domain. Mean goal attainment scaling scores (*T*-scores) will be calculated with a standard formula [38] for each measurement time point.

All analyses will be carried out according to the intention-to-treat principle using IBM SPSS statistics 22.0 for Macintosh. All tests of significance will report mean change and will be two-tailed, with α set at 0.05.

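### The sample size section claims 85% power at an effect size of 0.2 without naming the scale; 80 participants fits a 0.8 SD difference, and if 0.2 is a standardised mean difference the primary ANCOVA has about 14% power

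*Protocol article*

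**What the plan says.** The Sample size section says the number was based on earlier online intervention studies in dementia caregivers that used the self-efficacy scale (CSES), on "the use of repeated measures, within-between interaction with a mean effect size of 0.2", and on alpha 0.05 with "power 85 % and 25 % loss to follow-up". The result is 80 participants, 40 per arm. The section does not say whether 0.2 is Cohen's f, Cohen's d or something else. It also gives neither the number of measurements nor their correlation.

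The primary analysis is a different test. Under Quantitative measures, "an analysis of covariance (ANCOVA) will be conducted with post-intervention outcome as the dependent variable", with the baseline score and four further covariates, and "Group differences in the post-intervention outcome adjusted for its baseline value will be examined to test the primary hypothesis". If the groups differ, the difference is to be expressed as Cohen's *d*. Tests "will be two-tailed, with α set at 0.05".

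The Background gives two benchmarks, neither with a named scale. Earlier e-health studies in these caregivers affected confidence, stress, depression and "self-efficacy with effect sizes ranging from 0.2 to 0.3". Face-to-face support is credited with effects of 0.3 to 0.9 on self-efficacy.

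**The concern.** A reader who sees 0.2 drawn from online caregiver studies, 0.2 to 0.3 in the Background and Cohen's *d* in the analysis section will take the trial to be 85% powered for a small difference between arms. A trial of 80 looks far too small for that. In a repeated-measures interaction with two groups and two occasions, an f of 0.2 is not small on the *d* scale, so the same digit can stand for differences that are four-fold apart.

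What is at stake is how a non-significant 8-week result is read. Set against a claimed 85% power at 0.2, it would look like reasonable evidence that the programme has no small benefit. If the trial can only reliably detect a large difference, such a result would say little about a small one. The 8-week comparison carries this weight because controls receive the programme after it, so it is the only randomised contrast with no programme.

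**Working it through.** **Inputs from the document.** Effect size 0.2 (scale unnamed), two-sided alpha 0.05, power 85%, loss 25%, 80 enrolled 1:1. After 25% loss: 80 × 0.75 = 60 completers, 30 per arm.

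**Inputs assumed.** Two occasions and correlation 0.5 for the interaction test. For the ANCOVA, a baseline-to-8-week correlation r of 0.5, with a range of 0 to 0.7.

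**Step 1: reproduce 80.** For a within-between interaction with k groups, m occasions and correlation ρ:

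λ = f² · N · m / (1 − ρ), df1 = (k − 1)(m − 1), df2 = (N − k)(m − 1).

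With f = 0.2, k = 2, m = 2, ρ = 0.5:
- N = 58: λ = 0.04 × 58 × 2 / 0.5 = 9.28, power 84.9%.
- N = 60: λ = 0.04 × 60 × 2 / 0.5 = 9.60, power 86.1%.

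So 60 completers are needed, and 60 / 0.75 = 80 exactly. With the same f and ρ, 3, 4, 5 or 6 occasions give 64, 54, 48 or 43 enrolled, so among these only two occasions give 80.

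**Step 2: put f = 0.2 on the SD scale.** In a 2 × 2 layout the interaction deviation in each of the four cells is plus or minus one quarter of the between-arm difference in change. Hence f = d/4, and f = 0.2 means d = 0.8. With equal expected baselines under randomisation, this is a 0.8 SD difference at 8 weeks.

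Check: the SD of change is √(2(1 − 0.5)) = 1, so a *t* test on change has non-centrality 0.8 / √(2/30) = 3.10 = √9.60, the same test as in step 1.

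**Step 3: power of the primary ANCOVA.** Residual SD = √(1 − r²), non-centrality = d / (√(1 − r²) · √(2/30)), df = 60 − 7 = 53 (intercept, arm, baseline, four covariates). At r = 0.5 and d = 0.2: 0.2 / (0.866 × 0.258) = 0.89, power 14%.

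| True difference (SD) | r = 0 | r = 0.5 | r = 0.7 |
|---|---|---|---|
| 0.2 | 12% | 14% | 19% |
| 0.3 | 21% | 26% | 36% |
| 0.4 | 33% | 42% | 57% |
| 0.8 | 86% | 94% | 99% |

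The 0.4 row corresponds to 0.2 as an ordinary between-group f (d = 2f). With all 80 analysed, power at 0.2 SD and r = 0.5 is 17.5%.

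A simulation of 20,000 trials with 30 per arm and correlation 0.5, adjusting for baseline only, agrees. At 0.2 SD the power is 11.8% for the interaction and 14.1% for the ANCOVA. At 0.8 SD it is 85.8% and 93.4%.

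**Step 4: what 60 completers can do.** The difference detectable with 85% power is 0.68 SD at r = 0.5 (0.79 at r = 0, 0.56 at r = 0.7). The expected 95% confidence interval half-width at r = 0.5 is about 2.01 × 0.866 × 0.258 = 0.45 SD. For 85% power at 0.2 SD, the ANCOVA would need about 676 completers at r = 0.5 (roughly 900 enrolled), or a baseline-to-8-week correlation of about 0.97 with 60.

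**The case against.** The strongest reply is that nothing has been miscalculated. Read as the interaction f, 0.2 gives 80 exactly. At the 0.8 SD this implies, the ANCOVA does better than the sizing test (about 94% against 86%). That stands. A reader might infer that the 85% is an arithmetic error, or that sizing on one test and analysing with another weakens the trial. The figures support neither: at a given true difference the change of test is slightly favourable, and the shortfall exists only if 0.2 is not the interaction f.

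Nor can one say that 80 arises only from f = 0.2. Two occasions and correlation 0.5 are assumptions. An f of 0.1 also reaches about 85% with 60 completers, given five measurements at a correlation of about 0.78 or six at about 0.75, and the trial does have a longitudinal mixed model. That is not the primary test, however, so it does not supply power for the 8-week ANCOVA.

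A large effect is not excluded either. The programme includes face-to-face sessions, and the Background gives 0.3 to 0.9 for face-to-face support on self-efficacy. Against this, the Sample size section says its figure comes from online studies. The Background range of 0.2 to 0.3 has no named scale and a different citation from the 0.2 used for sizing, so treating the two as the same quantity is an inference.

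Finally, an article may leave the correlation and number of measurements to the full protocol. Their absence alone is not the point. The point is that a stated power figure can be read in two ways with very different consequences. Applying the full 25% loss at 8 weeks may be pessimistic, but with all 80 analysed power at 0.2 SD is still only 17.5%.

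**Conclusion.** The concern holds in conditional form. The claim of 85% power at 0.2 is sound if 0.2 is the interaction f, in which case the trial is sized for a 0.8 SD difference, roughly three to four times the 0.2 to 0.3 quoted for e-health if that range is in SD units. On the small-effect readings the claim fails for the primary ANCOVA: with 60 completers and r = 0.5, power is about 14% at 0.2 SD, 26% at 0.3 SD and 42% at 0.4 SD. The planned use of Cohen's *d* and the reliance on online studies make a small-effect reading natural, but the document does not settle it.

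It would therefore go too far to say that the trial simply has 14% power or that the sample size is wrong. The conclusion rests on 30 completers per arm and on the assumed correlation. No correlation from 0 to 0.7 lifts power at 0.2 SD above 19%.

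**What to change.** Keep 80 and rewrite the Sample size paragraph for the primary analysis, on a named scale, with the correlation declared as an assumption and shown as a range. For example:

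> Allowing for 25% loss, 80 participants give 60 completers (30 per arm). For the two-sided 0.05 ANCOVA of the post-intervention score, assuming a baseline-to-post correlation of 0.5, this gives 85% power for a between-arm difference of about 0.68 SD (0.79 to 0.56 SD for correlations of 0 to 0.7). Power at 0.2 to 0.3 SD is about 14% to 26%. The expected 95% confidence interval half-width is about 0.45 SD.

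State which metric the 0.2 was, and do not describe the trial as 85% powered for a 0.2 SD effect. Giving the interval width helps readers not to take a non-significant 8-week result as evidence against a small benefit.

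The cost is one paragraph and a less favourable power statement. It needs no extra participants and no change to the analysis.
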